### Randomisation and treatment allocation

Randomisations occur immediately once eligibility criteria are confirmed and informed consent is obtained. Participants are randomised twice simultaneously (figure 1, *factorial design*) using a web-based, electronic randomisation system controlled through an authorised username and password to:

**Figure 1 F1:**
[figure not shown]
Trial entry, randomisation and treatment. HD, high-dose; E, ethambutol; H, isoniazid; L, levofloxacin; R, rifampicin; TB, tuberculosis and Z, pyrazinamide. ˆ Target of 400. If planned recruitment to 400 is not possible, the modified target of 300 would be acceptable to allow 80% power and 350 to allow 85% power. * reduced mg/kg dosing used for children 25 kg and over. Both randomisations use minimisation with a random element and 1:1 allocation ratio.

6-month (24 weeks) intensive ATT regimen or a standard 12-month (48 weeks) ATT regimen in a 1:1 ratio (open-label).8 weeks of aspirin or matching placebo, in a 1:1 ratio (double-blinded).

Randomisation is a dynamic and concealed process; no preprepared lists are generated. Randomisation allocations are held securely within the Medical Research Council Clinical Trial Unit (MRCCTU) randomisation system and the Drug Supply Management System (DSMS). To randomise a participant, information is entered into an online trial database, and eligibility is automatically checked. On successful randomisation, the clinician prescribes allocated trial drugs. In all cases, neither the participant nor the investigator is notified of the treatment allocation of aspirin or placebo.

Aspirin and placebo are packed and prelabelled according to Good Manufacturing Practice guidelines with a code to maintain blinding for both trial site staff and participants recruited.

Since blinding of aspirin allocation is critical to the integrity of the study, all children are managed with the assumption that they receive aspirin. Unblinding during the trial is strongly discouraged unless it is a medical emergency and would alter clinical management. An emergency unblinding system for blinded randomisation can only be performed by a site principal investigator (PI) or allocated co-investigator through the DSMS. One unblinded delegated statistician has regular access to the treatment allocations for routine data querying and safety reporting purposes.

### Anti-TB regimen (randomisation 1)

All TB study drugs are fixed-dose combinations or paediatric dispersible formulations with the exception of levofloxacin (250 mg tabs) and pyrazinamide (400 mg tabs). Both the control and intervention arms use WHO-modified weight bands, which are adapted to achieve adequate doses and consistency across both treatment arms. In the intervention arm, children weighing >25 kg have a lower mg/kg target dosing compared with children <25 kg with isoniazid (10 mg/kg), rifampicin (20 mg/kg) and pyrazinamide (30 mg/kg) (online supplemental
table S2a and S2b (*intervention*) and online supplemental table 3a–3d (*control*)). All trial ATT drugs for all sites are manufactured by a single source.

### Adjunctive aspirin (randomisation 2)

Aspirin at a target dose of 20 mg/kg once daily for 8 weeks is dosed according to WHO-modified weight bands using dispersible aspirin 80 mg tablets. Placebo is matched in appearance, taste and odour. The same WHO-modified weight bands as for randomisation 1 are used (online supplemental
table S4).

### HIV co-infection

For children living with HIV, antiretroviral therapy (ART) is commenced within 4–8 weeks of ATT, unless already on treatment and in line with WHO guidance (the timing was adjusted from 2-8 weeks used at the start of the trial). ART is provided by country programmes, and drugs not recommended for simultaneous use with rifampicin are replaced with alternatives as per the WHO guidelines 2016. All children with TB and HIV co-infection receive cotrimoxazole prophylaxis for other infections and follow WHO/local guidelines on the use of any other prophylactic medications.

### Concomitant drug therapy

#### Adjunctive corticosteroids

All children receive either oral prednisolone at 2–4 mg/kg daily or oral dexamethasone at 0.3–0.6 mg/kg daily (or an equivalent dose of intravenous dexamethasone during inpatient stay), up to a maximum prednisolone dose of 60 mg/day in the first 4 weeks. The total course is 6–8 weeks, including gradual tapering of dose.

#### H2 receptor antagonist

Ranitidine prophylaxis is given for the first 8 weeks at 1 mg/kg three times per day (maximum per dose 3 mg/kg) for children aged 1–5 months, 2–4 mg/kg two times per day for those aged 6 months to 11.9 years (max 150 mg) and 300 mg at night-time for adolescents aged 12–18 years. If ranitidine is unavailable, cimetidine is used at 25–30 mg/kg/day in two divided doses for children aged ≥1 year and 20 mg/kg/day for children aged <1 year.

#### Pyridoxine supplementation

Pyridoxine (usually 5–12.5 mg/day) is given to children who are malnourished, adolescents and those receiving ART throughout treatment to prevent isoniazid-induced neuropathy.

### Study follow-up

Hospitalised participants are reviewed daily, with clinical progress, time to recovery from coma (Blantyre Coma Score) and other observations documented until discharge. All children return at weeks 4, 8, 16, 24, 36, 48 and 72 postrandomisation when ATT is dispensed, clinical assessments are performed, adherence and acceptability questionnaires are completed and AEs are assessed (online supplemental table S1b). Safety monitoring for toxicities using blood tests occurs at weeks 1, 2, 4 and 8 and at any other time points if clinically indicated. Clinical safety monitoring occurs at every follow-up visit. Total blood volumes and volumes required per study visit are considerably less than the blood volumes allowed for research in children internationally.^46^ Neurological function and neurocognitive assessment using mRS and Liverpool Outcome Score (LOS) are completed at weeks 24, 48 and 72. At these time points, urine is collected for pregnancy testing from all females >12 years of age or who have started menses, and HIV viral load testing is completed for children living with HIV.

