**Methods and analysis:**

The Shortened Intensive Therapy for Children with Tuberculous Meningitis (SURE) trial is a phase 3, randomised, partially blinded, factorial trial being conducted in Asia (India and Vietnam) and Africa (Uganda, Zambia and Zimbabwe). It is coordinated by the Medical Research Council Clinical Trial Unit at University College London (MRCCTU at UCL). 400 children (aged 29 days to <18 years) with clinically diagnosed TBM will be randomised, using a factorial design, to either a 24-week intensified regimen (isoniazid (20 mg/kg), rifampicin (30 mg/kg), pyrazinamide (40 mg/kg) and levofloxacin (20 mg/kg)) or the standard 48-week ATT regimen and 8 weeks of high-dose aspirin or placebo. The primary outcome for the first randomisation is all-cause mortality, and for the second randomisation is the paediatric modified Rankin Scale (mRS), both at 48 weeks. Nested substudies include pharmacokinetics, pharmacogenetics, pathophysiology, diagnostics and prognostic biomarkers, in-depth neurodevelopmental outcomes, MRI and health economics.

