### High-dose rifampicin

Rifampicin is critical in the early days of treatment, and high doses (eg, 35 mg/kg) are well tolerated.^22^,^24^ Pharmacokinetic (PK)-pharmacodynamic (PD) analyses show that higher exposures of rifampicin are essential to decrease time to culture conversion.^25^

Children have lower plasma exposure to rifampicin compared to adults with the same mg/kg dosing. Recent PK data from 100 Vietnamese children with TBM receiving a 10 mg/kg rifampicin dose found few with a target therapeutic plasma level, and nearly all had CSF concentrations well below the wild-type minimal inhibitory concentration (MIC).^26^ A small randomised trial in India and Malawi (TBM-KIDS, Tuberculous Meningitis in Kids study) used 30 mg/kg oral rifampicin daily, based on PK-PD modelling, showing that this dose was required to achieve optimal CSF rifampicin exposures in children.^27^ Further, in a paediatric PK and safety study (Opti-Rif, Optimizing Rifampicin Trial), 2 weeks of higher doses of rifampicin (up to 60–75 mg/kg) were safe and achieved target serum exposures.^28^ Although it is well known that children require higher mg/kg doses than adults to achieve target exposures, the safety of high rifampicin doses over longer durations is not yet established. Phase 3 trials evaluating the potential mortality benefit of high-dose rifampicin (30–35 mg/kg) are ongoing in adults and none in children (table 1).

**Table 1 T1:** Ongoing adult trials evaluating anti-TB drug regimens and adjunctive therapies in TBM

Trial and registry number	Population	Trial design	Study intervention	Setting	Sample size	Trial status
Anti-TB chemotherapy						
HARVEST ISRCTN15668391	Aged ≥18 yearsHIV co-infected and uninfected	Phase 3Randomised, parallelDouble-blindPlacebo-controlled	High-dose rifampicin (35 mg/kg) for 8 weeks	Indonesia, South Africa and Uganda	500 (planned)	Recruiting. Estimated completion—June 2025
ALTERNCT04021121	Aged >18 yearsHIV co-infected and uninfected	Phase 2Randomised, factorialOpen label	High-dose rifampicin (35 mg/kg) ANDLinezolid (1200 mg)for 4 weeks	Uganda	40	Recruitment completed. Results awaited
SIMPLENCT03537495	Aged ≥18 yearsHIV co-infected and uninfected	Phase 2Randomised, parallelOpen label	High-dose rifampicin (35 mg/kg) ANDLinezolid (600 mg or 1200 mg)for 14 days	Indonesia	36	Recruitment completed. Results awaited

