### Main study objectives

To determine whether the standard 12-month ATT regimen for treating paediatric TBM can be reduced, with similar efficacy and safety, to a 6-month intensified regimen of anti-TB drugs in children aged 29 days to less than 18 years.To determine whether adjunctive aspirin for 8 weeks of treatment reduces TBM-related neurodisability with minimal or no toxicity.

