### Secondary outcomes

Secondary efficacy and safety outcomes for both randomisations are detailed in table 2.

**Table 2 T2:** Secondary outcomes

Neurodevelopmental outcome	mRS at 24, 48 (randomisation 1) and 72 weeks.
Mortality	All-cause mortality at 72 weeks.
TB treatment failure	Clinical or microbiological relapse of TBM and/or TB disease at other sites by 72 weeks.
Specific AEs	Any grade 3 or 4 (as per DAIDs) clinical (including arthralgia and arthritis due to levofloxacin use) or laboratory AE. AE (any grade) leading to treatment modification. Gastrointestinal bleeding (any grade) due to increased risk with high-dose aspirin. DILI of grade 2 or more. Development of obstructive hydrocephalus. Tendonitis or tendon pain (any grade).
Acquired drug resistance	Drug resistance identified on genotypic/phenotypic DST—any suspected relapse with confirmed or suspected drug resistance.
Adherence to treatment	Adequate TB treatment adherence is defined as having taken at least 80% of doses.
Acceptability of treatment	Acceptability (taste, pill burden and drug administration) at 8, 24 and 48 weeks by the 4 group randomisation strata.
Viral load in children with HIV	Suppressed HIV viral load <50 copies/mL and change in CD4 count from baseline to 24, 48 and 72 weeks in children living with HIV.

AEadverse eventCD4CD4 T lymphyocyteDAIDsDivision of AIDS grading of severityDILIdrug-induced liver injuryDSTdrug susceptibility testingmRSmodified Rankin ScaleTBtuberculosisTBMtuberculous meningitis

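### Scheduled safety bloods end at week 8, before the regimens differ in number of drugs, so later laboratory toxicity and DILI are compared on clinically triggered, open-label testing

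*Protocol article*

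**What the plan says.** All places are in the protocol article.

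- **Main study objectives.** The first objective is to determine whether the standard 12-month regimen "can be reduced, with similar efficacy and safety, to a 6-month intensified regimen of anti-TB drugs".
- **Secondary outcomes, Table 2.** The safety outcomes include grade 3 or 4 laboratory adverse events and "DILI of grade 2 or more". Neither has a time window, whereas the mRS, mortality and relapse rows of the same table name weeks.
- **Study follow-up.** "Safety monitoring for toxicities using blood tests occurs at weeks 1, 2, 4 and 8 and at any other time points if clinically indicated". Clinic visits go on after that: "All children return at weeks 4, 8, 16, 24, 36, 48 and 72 postrandomisation", and "Clinical safety monitoring occurs at every follow-up visit".
- **Abstract and Introduction.** The intensified arm takes isoniazid, rifampicin, pyrazinamide and levofloxacin for 24 weeks. The standard regimen is four drugs for 2 months, then isoniazid and rifampicin for 10 months.
- **Study design.** Only the aspirin comparison is blinded. The anti-TB comparison is open-label.
- **High-dose rifampicin.** The background section notes that "the safety of high rifampicin doses over longer durations is not yet established".
- **Trial governance and committees.** A blinded central endpoint review committee reviews DILI of grade 2 and above and all serious adverse events.

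**The concern.** A laboratory-defined outcome can be counted only if blood is drawn. Up to week 8 both arms have the same minimum set of draws, so the chance of finding an event does not depend mainly on who suspects it. After week 8 a draw depends on a clinical decision by someone who knows which anti-TB regimen the child was allocated. The regimens begin to differ in number of drugs at that same point.

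If late events are missed equally in both arms, the observed difference shrinks towards the similarity that the objective hopes to show. If one arm is tested more readily, a difference may appear, disappear or reverse for that reason alone. A single count of DILI or laboratory adverse events to week 72 would not let a reader tell these apart, and it could be cited as evidence of similar laboratory safety over the whole intensified course.

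**Working it through.** The plan gives no figure on this point to reproduce. The check sets the blood-test schedule against the regimens.

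**Inputs.** Intensified: four drugs to week 24 (Abstract). Standard: four drugs for 2 months, then two (Introduction), 48 weeks in all (Abstract). Scheduled safety bloods: weeks 1, 2, 4 and 8; last visit at week 72 (Study follow-up). Two months is taken as 8 weeks.

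**Step 1: drugs by period.** Drug-weeks are number of drugs times weeks.

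| Weeks | Drugs, intensified v standard | Drug-weeks | Scheduled safety bloods |
|---|---|---|---|
| 0-8 | 4 v 4 | 4×8 = 32 v 4×8 = 32 | weeks 1, 2, 4, 8 |
| 8-24 | 4 v 2 | 4×16 = 64 v 2×16 = 32 | none |
| 24-48 | 0 v 2 | 0 v 2×24 = 48 | none |
| 48-72 | 0 v 0 | 0 v 0 | none |

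All of the difference in number of drugs falls after the last scheduled blood. Its direction also reverses: 64 − 32 = +32 drug-weeks for the intensified arm in weeks 8-24, then 0 − 48 = −48 in weeks 24-48. Pooling these periods would blur two opposite contrasts even with perfect detection. The count ignores dose. Doses also differ before week 8, but that period has scheduled bloods.

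**Step 2: time without scheduled bloods.**
- Intensified course: (24 − 8)/24 = 16/24 = 67%.
- Standard course: (48 − 8)/48 = 40/48 = 83%.
- Follow-up to week 72: (72 − 8)/72 = 64/72 = 89%.

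**Step 3: effect on a comparison after week 8.** Let p_I and p_C be the true risks of a laboratory-defined event after week 8 in the intensified and standard arms. Let s_I and s_C be the chances that such an event is tested for and found. The observed difference is D = s_I·p_I − s_C·p_C.
- Equal detection (s_I = s_C = s < 1): D = s(p_I − p_C), which is smaller in size than the true difference.
- Equal true risk (p_I = p_C = p): D = p(s_I − s_C), a difference produced by testing alone.
- Both unequal: D may be too large, too small or of the wrong sign.

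The documents give no late DILI rate and no detection probability, so no size for D is offered.

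**The case against.** The other side has several good points.

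- **Safety is still monitored after week 8.** Both arms are reviewed at weeks 16, 24, 36, 48 and 72, and serious adverse events are reported to week 72. Most Table 2 safety outcomes do not rest on blood tests alone: clinical grade 3 or 4 events, gastrointestinal bleeding, hydrocephalus, tendon symptoms. This stands. A reader might infer that nothing about safety can be concluded after week 8; the documents do not support that.
- **There is no outright contradiction.** An adverse-event outcome may include clinically triggered findings, and Table 2 does not promise scheduled testing to week 72. This stands. The issue is what the comparison can bear.
- **The rifampicin remark can be over-read.** It follows a study of 2 weeks of higher doses, so the unknown begins soon after week 2, and the week 4 and week 8 bloods cover part of it. It would be wrong to say that the whole unknown period lacks scheduled tests.
- **Blinded review of DILI limits arm-aware classification.** It does, but the committee can judge only events that were found.
- **The visit tables are in a supplement that is not shown, and analysis windows belong in the SAP.** If supplemental table S1b lists later safety bloods, it must be reconciled with the article's text. An analysis plan cannot restore tests that were not scheduled. Viral load sampling at weeks 24, 48 and 72 applies only to children with HIV and is not described as safety testing.

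**Conclusion.** The point holds for laboratory-defined and subclinical toxicity, including grade 2 or higher DILI found by blood test. Systematic detection covers weeks 0-8 only. It is absent for 67% of the intensified course and 83% of the standard course, which includes every week in which the arms differ in number of drugs. A pooled comparison to week 72 may be diluted or biased in either direction, and the documents do not show which.

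The gap does not touch the primary outcomes, serious adverse events or clinically apparent adverse events, although the last remain open to ordinary open-label influence. It might also seem to follow that a specific loss of power can be stated, or that bias must favour similarity. Neither is supported: the rates are unknown, late events could be very few, and unequal testing can act in both directions.

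The conclusion assumes that Study follow-up gives the full safety-blood schedule and that the control arm follows the regimen in the Introduction. It is a limit on a secondary safety claim, worth addressing because the remedy is cheap.

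**What to change.** 1. Present grade 3 or 4 laboratory adverse events and grade 2 or higher DILI by anti-TB arm, separately for weeks 0-8 (scheduled detection) and for weeks 8-24, 24-48 and 48-72 (clinically triggered detection).
2. In each period give, per arm, the number of children tested and the number of tests done.
3. State that any claim of similar laboratory-defined toxicity rests on systematic testing to week 8 only, and that later laboratory comparisons are descriptive.
4. Reconcile the blood-test schedule with the safety objective and the Table 2 outcomes. How that is done clinically is for the sponsor and investigators; no monitoring schedule is proposed here.

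Weeks 0-8 need not become the main laboratory safety analysis. That would move attention away from weeks 8-24, when the intensified arm carries the extra drugs. Showing the periods side by side is enough.

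The cost is some analysis wording, one more table and a narrower laboratory safety claim. Recruitment is complete and the table uses trial data, provided that unscheduled tests with normal results were also recorded; the article does not say. If they were not, the testing counts will be incomplete and the report should say so.

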### Functional outcome scoring

The paediatric mRS is used to assess gross motor function and has been recommended in a recent position paper on standardising TBM outcome measures.^47^ Additionally, the LOS—a simple screening questionnaire—is used to evaluate functional outcomes in all developmental domains. Neurological status and neurodevelopment at baseline are assessed with a short developmental history and completion of mRS and LOS on day 7 or at discharge, whichever is sooner. A full neurological examination is also completed at each follow-up.

### Quality of life questionnaires

Health outcomes are measured in quality-adjusted life years, with health-related quality of life measured using EQ-5D-Y, a generic health status instrument, which will be collected via proxy from a caregiver when the patient is cognitively or physically incapable (http://www.euroqol.org/eq-5d-products/eq-5d-y-youth.html). Data will be included in cost-effectiveness analyses in the health economics substudy (table 3).

**Table 3 T3:** Overview of nested SURE substudies

Substudy	Objective	Study design	Sites
Diagnostic and prognostic biomarkers*	Discover novel CSF, serum, urinary diagnostic and prognostic biomarkers or signatures using omic technology	Nested case-control, which prospectively recruits children with symptoms and/or signs of CNS infection but does not have TBM	200 controls: Zimbabwe and Zambia (100) and Vietnam (100)
PK	Determine whether the doses of anti-TB drugs, prescribed according to weight bands, result in appropriate drug plasma and CSF exposures	Intensive PK (n=36) in the intervention arm—six per PK grouped weight band.Sparse PK (n=108)—36 from the intervention arm (6/grouped weight bands) and 72 from the control arm (12/grouped weight bands).One CSF sample time-matched with plasma.All samples were taken on day 14 after autoinduction of rifampicin had occurred.Non-compartmental PK techniques and NONMEM.Penetration of TB drugs across the blood-CSF barrier; predictors of exposure will be assessed and relationships between exposures achieved and response will be assessed (PK-PD modelling).	Intensive PK—VietnamSparse PK—all sites
Pharmacogenetic	Evaluate genetic differences in drug metabolic pathways affecting TB drug exposure, including NAT-2	Store DNA/cell pellets from whole blood taken at any time during the study.	All sites
MRI	Evaluate the impact of aspirin on brain ischaemic changes between baseline and 6 months	MRI was performed at two time points using predetermined and standardised sequencing.Three independent radiologists blinded to the treatment arm and clinical condition review each MRI.	Vietnam (50 participants) and India (minimum 50 participants)
In-depth neurodevelopmental and neurocognitive studies	Explore the effect of treatment on neurodevelopmental outcomes	BSID for children under 3 years of age.Kaufmann Assessment Battery for children aged 3–18 years at 48 and 72 weeks.Together with mRS and LOS, the impact of disease severity at presentation on developmental domains will be determined.	Vietnam
Health economics†	Acceptability and health economic evaluations are conducted in the trial to help inform policy-making and scale up the implementation of the shortened-intensified anti-TB drug therapy if it is found to be non-inferior	Cost-effectiveness on trial comparisons, with health outcomes measured in QALYs and costs estimated from alternative perspectives (healthcare, patient/family, societal).Decision analytic modelling techniques will be used to synthesise evidence within the trial, with external evidence, to estimate impacts over the lifetime of patients.	All (analysis by University of York)
Epilepsy	Characterise frequency, type of seizure in the acute phase and epilepsy at 18 months follow-up.Factors associated with the development of epilepsy will be explored.	Seizure history, including number of antiseizure medications taken during hospitalisation and 18-month follow-up.The severity of epilepsy is determined using E-CHESS.Electroclinical syndrome will be reviewed by 2 paediatric neurologists.	India

* The diagnostic substudy slightly differs in time points for sample collection and follow-up between Zambia, Zimbabwe and Vietnam.

† In addition to health economics analysis at all sites, a cost-of-illness and social impact of TBM will be conducted to determine the impact on patients/families using a ‘one-on-one’ interview approach in India.

BSIDBayley Scales of Infant DevelopmentCNScentral nervous systemCSFcerebrospinal fluidE-CHESSEarly Childhood Epilepsy Severity ScaleLOSLiverpool Outcome ScoremRSmodified Rankin ScaleNAT-2N-acetyltransferase type 2NONMEMnon-linear mixed effects modellingPDpharmacodynamicPKpharmacokineticQALYsquality-adjusted life yearsTBtuberculosisTBMtuberculous meningitis

